In respect to nutritional intervention, particularly to optimize protein intake in advanced age, attention should be paid not only to the amount of proteins provided but also to their quality. Whey proteins have proved to enable a greater anabolic stimulation due to their faster digestion – resulting in a more rapid increase in plasma amino acid levels – and high content in essential amino acid. Among essential amino acids, leucine has been found to stimulate anabolism independently. It has been recommended that a per-meal anabolic threshold of essential amino acids, particularly in terms of leucine (2.5–2.8 g/meal), should be achieved at least twice daily. Besides, vitamin D supplementation was found to result in improved muscle strength, particularly in old adults with low serum levels of the vitamin, and to promote muscle anabolism also through a positive interaction among all these nutrients.

Recent studies have demonstrated that the use of a muscle-targeted food for special medical purposes (a mixture of whey proteins enriched with essential amino acids, especially leucine, vitamin D and calcium) improves muscle mass and strength. However, although clinical trials in sarcopenia should address the recovery of physical functioning, the efficacy of the muscle-targeted food for special medical purposes on physical performance has never been evaluated in combination with physical exercise in a high-quality trial. Furthermore, there are no data on the economic benefits deriving from nutritional support in in-patient rehabilitation facilities.

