***2.2 Secondary endpoints***

The following key secondary endpoints (change per month in physical performance outcome measures) will be investigated:

- chair-stand test
- Timed up and go (TUG) test
- Short Physical Performance Battery (SPPB)

The following secondary endpoints will be also addressed:

- change per month in handgrip strength
- change per month in Tinetti scale
- change per month in Barthel Index
- change per month in activities of daily living (ADL) score
- change per month in body weight
- change per month in appendicular muscle mass (AMM)
- change per month in skeletal muscle mass index (SMMI)
- change per month in cognitive status (Trail making test and Mini Mental State Examination [MMSE])
- change per month in quality of life (Short-Form 12-Item Health Survey [SF-12])
- the proportion of patients who improved their rehabilitation intensity profile
- the modality of discharge (home vs. institution)
- the overall economic benefits (using length of stay [LOS] and total duration of rehabilitation [minutes] as surrogate measures)
- safety of the intervention

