# **Intervention**

## *5.1 Physical intervention*

An individualized, moderate-level (Borg Rate of Perceived Exertion scale score of 12-14) physical fitness and muscle mass promoting program will be set up for all in-patients. Trained staff will supervise all exercise sessions, monitoring the individual exercise ability of each patient and adjusting the intensity level, as appropriate. The intervention will consist of exercise sessions daily, 5 times/week. The initial duration of each session will be 20 minutes and it could be increased progressively, along with the intensity of the exercises, up to 30 minutes. All sessions will include the following:

- 5-minute warm-up

- 5-to-10-minute progressive sequence from seated to standing muscle-strengthening exercises: toe raises, heel raises, knee lifts, knee extensions in the seated position; hip flexions and lateral leg raises standing next to a chair used for stability; ankle-weight bearing exercises (seated knee flexion and extension, standing knee flexion and extension), with weights ranging from 0.5 to 1.5 kg as appropriate (in accordance with each participant’s strength as the resistance progressively increased); leg extensions and hip flexions using resistance bands. Upper-body exercises will be also performed and included double-arm pull downs and biceps curls. Patients will be asked to perform up to 8 repetitions, as appropriate

- 5-to-10-minute balance and gait exercises: one-leg stands, tandem stands, multidirectional weight shifts, tandem walk, as well as practicing proper gait mechanics focusing on balance maintenance and increasing stride length, while changing direction and/or gait pattern

- 5-minute cool-down.

The minimum duration of the physical intervention program will be 4 weeks and it could be prolonged up to 8 weeks according to the results obtained. Specifically, the decision to finish the rehabilitation and to discharge the patient will be taken by a multidisciplinary team (geriatrician, physiatrist, physiotherapist and nurse) once the duration of each exercise session is stabilized to 30 minutes and no increase in intensity could be considered for 5 consecutive days.

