***5.2 Nutritional intervention***

An individualized dietary program will be drawn up for each patient, taking nutritional and mastication issues, as well as any swallowing issues into consideration. In addition to hospital diet, subjects will be randomly allocated to receive twice daily:

a) Experimental formula: a whey protein-based food for special medical purposes enriched with leucine and vitamin D (Fortifit®, Nutricia). Each serving consists of 40 g of powder (vanilla or strawberry flavor), providing 150 kilocalories and containing 20 g of whey proteins, 2.8 g of leucine, 9 g of carbohydrates, 3 g of fat, 800 IU of vitamin D, and a mixture of vitamins, minerals (calcium, 500 mg), and fibers [17-20].

b) Control formula: an isocaloric formula consisting of 40 g of a flavored (vanilla or strawberry) powder containing maltodextrins.

The intervention formula will be reconstituted with 100-150 mL water and administered at breakfast and in the afternoon. In the event of dysphagia to liquids, the density of the reconstituted formula will be increased, as appropriate.

The actual supplement and control formula will be given in identical containers devoid of any labelling for at least 4 weeks (minimum duration of the rehabilitation) up to 8 weeks (maximum duration of the rehabilitation). Compliance with intake of nutritional interventions will be monitored by recording the number of servings consumed every day in a diary.

1. **Methods**

The assessments and the procedures to be performed throughout the study are summarized in the following table:

| ASSESSMENTS/PROCEDURES | BASELINE | END OF STUDY |
| --- | --- | --- |
| Inclusion/exclusion criteria | X |  |
| Informed consent | X |  |
| Medical history & demographics | X |  |
| Randomization | X |  |
| Anthropometry | X | X |
| Protein-calorie intake | X | X |
| Mini Nutritional Assessment | X | X |
| Physical performance | X | X |
| Physical function | X | X |
| Muscle strength (handgrip) | X | X |
| Muscle mass | X | X |
| Cognitive function | X | X |
| Biochemistry | X | X |
| Quality of life | X | X |
| Complexity of assistance needs | X | X |
| Compliance to nutritional intervention |  | X |
| Safety data |  | X |
| Modality of discharge |  | X |
| Total duration of rehabilitation |  | X |
| Length of stay |  | X |

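### The economic secondary endpoint counts only length of stay and rehabilitation minutes; without the cost of the formula it can show resource use but not an overall economic benefit

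*Protocol*

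**What the plan says.** Section 2.2 names the endpoint and its components together: "the overall economic benefits (using length of stay [LOS] and total duration of rehabilitation [minutes] as surrogate measures"). No unit cost, product cost or other resource item is part of it. Modality of discharge is a separate secondary endpoint.

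The Introduction gives an economic motive, saying that "there are no data on the economic benefits deriving from nutritional support in in-patient rehabilitation facilities".

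Section 5.2 gives the experimental or control formula twice daily over the whole programme. It also says: "Compliance with intake of nutritional interventions will be monitored by recording the number of servings consumed every day in a diary".

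Section 5.1 sets the length of the programme: "The minimum duration of the physical intervention program will be 4 weeks and it could be prolonged up to 8 weeks". It ties stay to that programme, because "the decision to finish the rehabilitation and to discharge the patient will be taken by a multidisciplinary team", and this happens "once the duration of each exercise session is stabilized to 30 minutes and no increase in intensity could be considered for 5 consecutive days". Sessions take place 5 times a week; they start at 20 minutes and may lengthen to 30 as the patient progresses.

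Sections 6.2 and 8.2 both anticipate a treatment effect on stay. Section 8.2 reports a treatment effect with a 95% confidence interval for all endpoints.

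**The concern.** An overall economic benefit is a balance: what the intervention saves, less what it costs. Both chosen measures lie on one side of that balance. The formula is the only resource that the experimental arm receives by design and that routine care would have to pay for, and it enters neither measure. A shorter stay in the experimental arm could therefore be reported under the heading of an overall benefit even if the product cost more than the bed-days it saved. Nothing in the endpoint's definition would reveal this.

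The Introduction presents the lack of economic data as a gap, so readers are likely to use this result for that question.

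There is a second, smaller point. The programme cannot end before week 4 or run beyond week 8, and its end is decided together with discharge. Length of stay therefore inherits those limits, and its result needs to be read with them in view.

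**Working it through.** **1. The protocol's own figure.** None is given for the economic endpoint. The only calculated figure is the sample size in section 8.1. For effect size 0.5, two-sided 5% and 80% power, the two-sample t-test needs 63.8, so 64 per arm (power 0.801 at 64). This agrees with the protocol and plays no part in what follows.

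**2. Formula exposure** (sections 5.1 and 5.2). Servings per patient = 2 per day × days:
- 4 weeks: 2 × 28 = 56
- 8 weeks: 2 × 56 = 112

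These counts assume full compliance; the diary gives the actual number.

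**3. What leaving them out could mean.** Let L be the stay in days in the experimental arm and r the price of one serving as a fraction of the cost of one bed-day. The protocol does not give r; the range 0.5% to 3% is assumed. With therapy minutes equal in the two arms, the shortening of stay needed to pay for the formula is

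break-even days = 2 × L × r

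| L (days) | r = 0.5% | r = 1% | r = 2% | r = 3% |
|---|---|---|---|---|
| 28 | 0.28 | 0.56 | 1.12 | 1.68 |
| 42 | 0.42 | 0.84 | 1.68 | 2.52 |
| 56 | 0.56 | 1.12 | 2.24 | 3.36 |

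A shortening of stay below the relevant entry would look favourable on the endpoint as defined, yet would be a net cost. At the low end the omission is small; at the high end it is not. The protocol gives no expected size for the effect on stay, so it does not show that the formula's cost is negligible.

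**4. Range of the minutes measure** (section 5.1).
- Lower limit: 4 weeks × 5 sessions × 20 min = 400 min. If the last five sessions are at 30 min, it is 15 × 20 + 5 × 30 = 450 min.
- Upper limit: 8 × 5 × 30 = 1,200 min.

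At an equal 4-week stay, with an assumed linear rise from 20 to 30 min, a patient who reaches 30 min in one week accrues 570 min. One who takes three weeks accrues 520 min, so the faster patient uses 50/520, or about 10%, more. That is therapist time actually used, so it belongs in a resource count.

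**5. The 4-to-8-week window.** Assume that time to readiness for discharge is normal with mean μ and SD σ (weeks), that treatment shortens it by δ, and that stay is this time clamped to [4, 8]. With α = (4 − μ)/σ and β = (8 − μ)/σ, mean stay is

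m(μ) = 4Φ(α) + 8[1 − Φ(β)] + μ[Φ(β) − Φ(α)] − σ[φ(β) − φ(α)]

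The share of the true shortening that is visible in stay is [m(μ) − m(μ − δ)]/δ.

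| μ | σ | δ | Share visible | Ready before week 4, control / experimental |
|---|---|---|---|---|
| 6 | 0.5 | 1 | 100% | 0% / 2% |
| 6 | 1 | 1 | 92% | 2% / 16% |
| 6 | 2 | 1 | 66% | 16% / 31% |
| 4.5 | 1 | 1 | 50% | 31% / 69% |
| 4.5 | 2 | 1 | 48% | 40% / 60% |

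Over the assumed range (μ 4.5 to 7, σ 0.5 to 2, δ 0.5 or 1), 48% to 100% is visible. The answer depends on how many patients sit at the bounds, which the protocol does not say.

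**The case against.** The protocol calls the two measures surrogates and never uses the word net. The study aim in section 2 does not mention economics, and the Introduction says only that data are lacking; a randomised comparison of stay would supply some. Unit prices and costing methods are often left to a later document, and servings are already recorded, so the product's cost could be added without touching trial conduct.

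Much of this stands, and it limits the weight of the point. It does not remove it. The endpoint's name and its two components are both fixed in section 2.2, and a surrogate with no term for the intervention's cost cannot show the sign of the overall balance.

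A reader might infer more than the documents support:

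- *That the endpoint understates any faster recovery.* It does not: a gain wholly inside weeks 4 to 8 is measured in full. Bed-days actually used are also the right quantity for resource use, whenever the patient became ready. What cannot appear is a saving from readiness before week 4.
- *That minutes run the wrong way because sessions lengthen as patients improve.* A patient given longer sessions does use more therapist time. Two resource items moving in opposite directions is not an error. A contrast as wide as 450 against 590 minutes (20 + 19 × 30), or 31%, needs a jump to 30 minutes after one session, while section 5.1 describes a progressive increase.
- *That stay can only be read as a saving.* Testing is two-sided and section 8.2 reports confidence intervals, so a longer stay would show. What is missing is the formula's cost.

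**Conclusion.** The point holds as a mismatch between the endpoint's label and its content. With length of stay and rehabilitation minutes alone, the trial can report a difference in care resources used. It cannot say whether the overall economic balance is favourable, because 56 to 112 servings per patient are left out.

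The size in money is unknown from the protocol. Under the assumed price range of 0.5% to 3% of a bed-day per serving, the omission is worth 0.42 to 2.52 bed-days for a 42-day stay. That figure rests on full compliance and equal therapy minutes in the two arms.

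The 4-to-8-week window is a matter of interpretation. It may hide part of a true gain in readiness, but by how much cannot be told from the document.

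This is one secondary endpoint, outside the key secondary group.

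**What to change.** In sections 2.2 and 8.2:

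1. Report length of stay and rehabilitation minutes as separate resource-use results.
2. Define the economic endpoint as the between-arm difference in cost per patient: stay and minutes valued at the facility's rates, plus, in the experimental arm, the servings in the diary at the product's price. Report the mean difference with its 95% confidence interval. The control powder serves the blinding, so it need not be charged.
3. If unit prices are not used, rename the endpoint *resource use (LOS, rehabilitation minutes)* and draw no conclusion on overall economic benefit.
4. Report the share of patients in each arm whose programme ended at 4 weeks and at 8 weeks, and state that savings from readiness before week 4 cannot appear in stay.

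No change to the duration or discharge rule is implied. An analysis of time to first meeting the discharge criterion is not proposed: the assessment table in section 6 lists only total duration and length of stay, and no dated session-level record of duration and intensity is described.

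The cost is a change of wording, unit prices from the facility and the supplier, and a tabulation from data already planned. There are no new visits or procedures. The downside is that the economic result may look less favourable once the formula is charged.

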***2.3 Other pre-specified study endpoints***

As explorative endpoints, we will also consider changes (per month) in: protein and energy intake, Mini Nutritional Assessment (MNA®) score, C-reactive protein, vitamin D, total cholesterol, albumin and creatinine.

# **Study design**

A single-site, interventional, randomized (1:1), parallel-group, double-blind, controlled, 8-week clinical trial.

Expected study duration: 24 months.

# **Participants**

Consecutive, old adults, candidates for in-patient rehabilitation, who were found to have sarcopenia.

## *4.1 Inclusion criteria*

- age ≥65 years
- admission for physical rehabilitation
- sarcopenia (according to European Working Group on Sarcopenia in Older People [EWGSOP] criteria in terms of outcome of body composition by bioimpedance analysis [skeletal muscle mass/body weight  100, ≤37% in men and ≤28% in women], handgrip strength and gait speed)
- Mini Mental State Examination (MMSE) ≥18
- Written informed consent (patient or legal guardian)

## *4.2 Exclusion criteria*

- Any malignant disease during the last five years
- Known kidney failure (previous glomerular filtration rate <30 ml/min);
- Known liver failure (Child-Pugh class B or C)
- Known psychiatric disorder
- Endocrine disorders associated with disorders of calcium metabolism (except osteoporosis)
- Indications related to the study product:
  - - More than 10 µg (400 IU) of daily Vitamin D intake from medical sources
    - More than 500 mg of daily calcium intake from medical sources.
    - Adherence to a high energy or high protein diet up or use of protein containing or amino acid containing nutritional supplements up to three months before starting the study.
- Known allergy to milk, milk products or other components of the proposed interventions
- Indication to or ongoing artificial nutrition support
- Inclusion in other nutrition intervention trials
- Investigator's uncertainty about the willingness or ability of the subject to comply with the protocol requirements
- Refusal

# **Intervention**

## *5.1 Physical intervention*

An individualized, moderate-level (Borg Rate of Perceived Exertion scale score of 12-14) physical fitness and muscle mass promoting program will be set up for all in-patients. Trained staff will supervise all exercise sessions, monitoring the individual exercise ability of each patient and adjusting the intensity level, as appropriate. The intervention will consist of exercise sessions daily, 5 times/week. The initial duration of each session will be 20 minutes and it could be increased progressively, along with the intensity of the exercises, up to 30 minutes. All sessions will include the following:

- 5-minute warm-up

- 5-to-10-minute progressive sequence from seated to standing muscle-strengthening exercises: toe raises, heel raises, knee lifts, knee extensions in the seated position; hip flexions and lateral leg raises standing next to a chair used for stability; ankle-weight bearing exercises (seated knee flexion and extension, standing knee flexion and extension), with weights ranging from 0.5 to 1.5 kg as appropriate (in accordance with each participant’s strength as the resistance progressively increased); leg extensions and hip flexions using resistance bands. Upper-body exercises will be also performed and included double-arm pull downs and biceps curls. Patients will be asked to perform up to 8 repetitions, as appropriate

- 5-to-10-minute balance and gait exercises: one-leg stands, tandem stands, multidirectional weight shifts, tandem walk, as well as practicing proper gait mechanics focusing on balance maintenance and increasing stride length, while changing direction and/or gait pattern

- 5-minute cool-down.

The minimum duration of the physical intervention program will be 4 weeks and it could be prolonged up to 8 weeks according to the results obtained. Specifically, the decision to finish the rehabilitation and to discharge the patient will be taken by a multidisciplinary team (geriatrician, physiatrist, physiotherapist and nurse) once the duration of each exercise session is stabilized to 30 minutes and no increase in intensity could be considered for 5 consecutive days.

***5.2 Nutritional intervention***

An individualized dietary program will be drawn up for each patient, taking nutritional and mastication issues, as well as any swallowing issues into consideration. In addition to hospital diet, subjects will be randomly allocated to receive twice daily:

a) Experimental formula: a whey protein-based food for special medical purposes enriched with leucine and vitamin D (Fortifit®, Nutricia). Each serving consists of 40 g of powder (vanilla or strawberry flavor), providing 150 kilocalories and containing 20 g of whey proteins, 2.8 g of leucine, 9 g of carbohydrates, 3 g of fat, 800 IU of vitamin D, and a mixture of vitamins, minerals (calcium, 500 mg), and fibers [17-20].

b) Control formula: an isocaloric formula consisting of 40 g of a flavored (vanilla or strawberry) powder containing maltodextrins.

The intervention formula will be reconstituted with 100-150 mL water and administered at breakfast and in the afternoon. In the event of dysphagia to liquids, the density of the reconstituted formula will be increased, as appropriate.

The actual supplement and control formula will be given in identical containers devoid of any labelling for at least 4 weeks (minimum duration of the rehabilitation) up to 8 weeks (maximum duration of the rehabilitation). Compliance with intake of nutritional interventions will be monitored by recording the number of servings consumed every day in a diary.

1. **Methods**

The assessments and the procedures to be performed throughout the study are summarized in the following table:

| ASSESSMENTS/PROCEDURES | BASELINE | END OF STUDY |
| --- | --- | --- |
| Inclusion/exclusion criteria | X |  |
| Informed consent | X |  |
| Medical history & demographics | X |  |
| Randomization | X |  |
| Anthropometry | X | X |
| Protein-calorie intake | X | X |
| Mini Nutritional Assessment | X | X |
| Physical performance | X | X |
| Physical function | X | X |
| Muscle strength (handgrip) | X | X |
| Muscle mass | X | X |
| Cognitive function | X | X |
| Biochemistry | X | X |
| Quality of life | X | X |
| Complexity of assistance needs | X | X |
| Compliance to nutritional intervention |  | X |
| Safety data |  | X |
| Modality of discharge |  | X |
| Total duration of rehabilitation |  | X |
| Length of stay |  | X |

## *6.1 Assessments*

The following assessments will be performed throughout the study as indicated above:

*Medical History & Demographics.* Information will be collected on age, gender, main admission diagnosis, number of comorbidities and medications.

*Nutritional Assessment:* body weight (to the nearest 0.1 kg) and height (to the nearest 0.5 cm) will be measured according to standard procedures and body mass index (BMI) will be derived accordingly (*Anthropometry*). A trained dietitian will be responsible for the evaluation of calorie and protein intake. At study inclusion a 24-h dietary recall (with the aid of the caregiver) will be performed with the help of a food atlas, while at the end of study a calibrated dietetic spring scale will be used to weigh all foods served and returned on consecutive days. A computer program (DR3 v3.1.0; Sintesi Informatica Srl, Milano, Italy) will be used to estimate the energy and the macronutrient content of food consumed (*Protein-calorie intake*), including nutritional supplementation. Finally, nutritional status will be rated by means of the *Mini Nutritional Assessment* (MNA®), a brief questionnaire based on an anthropometric assessment (BMI and weight loss), a general assessment (lifestyle, medication, and mobility), and a dietary assessment (number of meals, food and fluid intake, self-assessment of autonomy of eating, and self-perception of health and nutrition).

*Muscle mass (body composition)*: in the screening phase, the presence of low skeletal muscle mass will be diagnosed [(skeletal muscle mass/body weight  100) ≤37% in men and ≤28% in women] using bioelectric impedance analysis (BIA 101; Akern s.r.l., Florence, Italy). Then, appendicular muscle mass (AMM) and total body skeletal muscle mass (for the calculation of skeletal muscle mass index [SMMI]) will be evaluated using Dual-energy X-ray absorptiometry (DXA; Lunar Prodigy, GE Medical Systems).

*Evaluation of physical performance*: it will comprise multiple tests. Gait speed will be evaluated by the 4-meter walking test. Lower body leg strength and endurance will be investigated through the chair-stand test (time required to rise 5 consecutive times from a chair without arm rests). Composite evaluation of mobility, balance, walking ability, and fall risk will be performed using the Timed up and go (TUG) test, which assesses the time taken to rise from an arm chair, walk 3 meters, turn, walk back, and sit down again. Finally, we will consider the Short Physical Performance Battery (SPPB) which consists of 3 components: gait speed, chair-stand test, TUG, and balance (3 different tests assessing ability to stand with the feet together in the side-by-side, semi-tandem, and tandem positions). Accordingly, each component is scored from 0 (not possible) to 4 (best performance); the scores add up to a total score ranging from 0 to 12.

*Functional status evaluation*: it will include muscle strength measured as handgrip strength (according to standard procedures by a hydraulic hand dynamometer [Jamar 5030J1; Sammons Preston Rolyan; Bolingbrook, Canada]; accuracy 0.6 N]), the Barthel Index (BI; covering all the aspects of self-care independence in daily living activities including transfer, walking, stairs, toilet use, dressing, feeding, bladder, bowel, grooming, bathing; score range, 0 [completely dependent] - 100 [complete self-sufficiency]), activities of daily living (ADL) score, and the Tinetti scale which measures characteristics associated with falls, assessing balance (14 items; 24 points) and gait (10 items; 16 points) for a total score up to 40 (the higher the score, the better the performance).

*Evaluation of cognitive functions*: it will include the MMSE (a 30-point questionnaire used to measure cognitive impairment assessing functions including registration, attention and calculation, recall, language, ability to follow simple commands and orientation) and the Trail making test a neuropsychological test of visual attention and task switching, providing information about visual search speed, scanning, speed of processing, mental flexibility, as well as executive functioning (the score is obtained as the number of seconds needed to complete the test).

*Quality of life assessment*: participants will be tested with the Short-Form 12-Item Health Survey (SF-12), a short, generic health‐status measure reproducing the 2 summary scores of the SF‐36 - the physical component summary (PCS) score and the mental component summary (MCS) score – by addressing 8 health domains (physical functioning, role physical, bodily pain, general health, vitality, social functioning, role emotional, and mental health.

*Biochemical assessment*: venous blood samples will be drawn after an over-night fast and used for the evaluation of routine parameters (total blood count, glucose, transaminases, albumin, creatinine, blood urea nitrogen, serum electrolytes, transferrin, total cholesterol), as well as C-reactive protein and 25-hydroxyvitamin D (25(OH)D) levels.

*Assessment of complexity of assistance needs*: the rehabilitation profile system will be used to rate the complexity of assistance needed by the patient. Profiles are defined according to the assessment of 4 kinds of intervention and their interaction (general assistance, functional reactivation and recovery, medical support and social support). Patients entering an intermediate rehabilitation program as in-patients can be assigned any one of 5 different profiles:

- Profile 1: low assistance and medical needs; patient requires mainly general assistance;
- Profile 2: intermediate general assistance needs, but low medical needs; patient requires mainly general assistance, as well as functional reactivation and recovery;
- Profile 3: high general assistance needs and intermediate medical needs; patient requires mainly general assistance, functional reactivation and recovery, as well as intermediate medical support;
- Profile 4: high assistance and medical needs; patient requires general assistance, functional reactivation and recovery, as well as medical support on account of important concomitant diseases;
- Profile 4B DEMENTIA: high assistance and medical needs. Patient suffers from dementia and therefore requires a lot of general assistance, functional reactivation and recovery, as well as medical and social support provided by highly trained professionals.

